**Methods:**

This is a multicenter randomized sham-controlled clinical trial. We will allocate 252 subjects aged between 45 and 75 years diagnosed with motor aphasia after stroke with an onset time ranging from 15 to 90 days into two groups randomly in a 1:1 ratio. Patients in the experimental group will be treated with “Xing-Nao Kai-Qiao” acupuncture therapy plus language training, and those in the control group will be treated with sham-acupoint (1 cun next to the acupoints) acupuncture therapy plus language training. All the patients will be given acupuncture and language training for 6 weeks, with a follow-up evaluation 6 weeks after the end of the treatment and 6 months after the onset time. The patients will mainly be evaluated using the Western Aphasia Battery and Chinese Functional Communication Profile, and the incidence of treatment-related adverse events at the 2nd, 4th, and 6th weeks of treatment will be recorded. The baseline characteristics of the patients will be summarized by group, the chi-squared test will be used to compare categorical variables, and repeated measures of analysis of variance or a linear mixed model will be applied to analyze the changes measured at different time points.

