### Trial design {8}

The clinical study is designed as a multicenter randomized sham-controlled clinical trial. A total of 252 participants will be randomized into two parallel groups at a 1:1 ratio, including the acupuncture group and the sham acupuncture group. Each eligible subject will undergo a 6-week treatment period, followed by a follow-up period of 6 weeks after treatment and 6 months after onset time. Six visits in total are scheduled for each subject at weeks 0, 2, 4, and 6; 6 weeks after treatment; and 6 months after onset time (Table 2).

**Table 2 Tab2:** Trial process chart

Period		Screening	Treatment			Follow-up	
Items		Before enrolment (weeks) −2 to −1	End of 2-week treatment (weeks) 3	End of 4-week treatment (weeks) 5	End of 6-week treatment (weeks) 7	End of 6 weeks after the end of the treatment follow-up (weeks) 13	End of 6 months after the onset time follow-up
Recruitment		X					
Enrolment		X					
Inclusion criteria		X					
Exclusion criteria		X					
Basic characteristic variables		X					
Randomization and allocation concealment		X					
Primary outcomes	Western Aphasia Battery	X	X	X	X	X	X
	Chinese Functional Communication Profile	X	X	X	X	X	X
Secondary outcomes	X	X	X	X		X	X
	National Institute of Health Stroke Scale	X	X	X	X	X	X
	Stroke and Aphasia Quality of Life Scale-39	X	X	X	X	X	X
	Stroke Specific Quality of Life Scale	X	X	X	X	X	X
	Health Scale of Traditional Chinese Medicine	X	X	X	X	X	X
Adverse events recorded			X	X	X		
Relapse						X	X
Self-reported drug therapy			X	X	X	X	X
Compliance			X	X	X		

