### Outcomes {12}

#### Primary outcomes

The main observation was the difference between the two groups in WAB [17] scale scores and CFCP [18] scale scores after 6 weeks of treatment to assess the patients’ language abilities and functional communication abilities.

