#### Secondary outcomes

The secondary outcome measures were WAB scale scores and CFCP scale scores, assessing the difference between the two groups at 6 months after onset time; Boston Diagnostic Aphasia Examination (BDAE) [19] scores for the severity of the language competence status; Stroke and Aphasia Quality of Life Scale-39 (SAQOL-39) [20] and Stroke-Specific Quality of Life Scale (SS-QOL) [21] scores for the quality of living in stroke patients; National Institute of Health Stroke Scale (NIHSS) [22] scores for the neurological deficit; Health Scale of Traditional Chinese Medicine (HSTCM) [23] scores for the health status, assessing the difference between the two groups after 6 weeks of treatment and 6 months after onset time. The study’s adverse events and dropout causes will be recorded in a case report form (CRF).

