## Statistical methods

### Statistical methods for primary and secondary outcomes {20a}

Baseline characteristics of patients were summarized in groups according to the study data. The chi-square test was used to compare categorical variables, and the 2-sample *t*-test or Wilcoxon rank-sum test was used to compare continuous variables. Analysis of variance for repeated measures was applied according to the outcome of the measurement time, or linear mixed models were used to analyze changes in measurements at different time points. Covariates such as age, duration of illness, and severity of aphasia will be included in the statistical model, correcting the effects of possible imbalances. If there is a violation of the distribution assumption, the appropriate transformation will be used.

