### Methods in analysis to handle protocol non-adherence and any statistical methods to handle missing data {20c}

Data may be missing. Therefore, we will analyze data based on intention-to-treat analysis (ITT) and per-protocol analysis (PP) principles. We will also assess the robustness of the results of our research by comparing the results of the two datasets mentioned above to evaluate group effects.

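### The primary outcome is a week-6 group difference, but the stated analysis is repeated-measures ANOVA or a mixed model across time points, with no rule for choosing and no week-6 contrast

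*Protocol article*

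**What the plan says.** All references are to the protocol article.

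- **Primary outcomes {12}** sets one time point: the "difference between the two groups in WAB [17] scale scores and CFCP [18] scale scores after 6 weeks of treatment".
- **Secondary outcomes {12}** places the later WAB and CFCP scores among the secondary measures, "assessing the difference between the two groups at 6 months after onset time".
- **Sample size {14}** assumes one after-treatment WAB-AQ difference of 10.9, a standard deviation of 22.9 in both groups, a superiority margin of 3, 80% power and an alpha of 0.05. It arrives at 105 per group and 252 enrolled.
- **Statistical methods for primary and secondary outcomes {20a}** states: "Analysis of variance for repeated measures was applied according to the outcome of the measurement time, or linear mixed models were used" to analyse changes across time points. It adds age, duration of illness and severity of aphasia as covariates. An earlier sentence, next to the one on baseline summaries, says "the 2-sample *t*-test or Wilcoxon rank-sum test was used to compare continuous variables".
- **The abstract** repeats the alternative: "repeated measures of analysis of variance or a linear mixed model will be applied to analyze the changes measured at different time points".
- **Trial design {8}**: "Six visits in total are scheduled for each subject at weeks 0, 2, 4, and 6; 6 weeks after treatment", with a sixth visit 6 months after onset. Table 2 schedules WAB and CFCP at all six.
- **Section {20c}** concedes that data may be missing and says "we will analyze data based on intention-to-treat analysis (ITT) and per-protocol analysis (PP) principles". It names no imputation.

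**The concern.** A primary outcome at one time point needs an analysis that returns the group difference at that time point. The article offers two methods that answer different questions and treat missing visits differently, and links neither to week 6.

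On the ANOVA branch the usual outputs are a group effect, a time effect and a group-by-time test. The group effect is an average over the analysed visits, including baseline, where randomisation makes the expected difference zero. The group-by-time test says only that the two profiles differ somewhere. Neither is the quantity on which the trial was sized, and neither can be compared with the margin of 3.

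The branches also differ in who is analysed. Classical repeated-measures ANOVA needs a complete row per patient. A likelihood-based mixed model uses whatever scores are available. On the first branch, a patient with a valid week-6 score can be lost because of a different missed visit.

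At stake is which number is reported as the primary result, and on how many patients.

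**Working it through.** **1. What the sample size targets.** Inputs from Sample size {14}: difference 10.9, margin 3, SD 22.9, alpha 0.05, power 80%.

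n per group = 2 × (z₁₋α + z₁₋β)² × SD² / (10.9 − 3)²

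With one-sided alpha: 2 × (1.645 + 0.842)² × 22.9² / 7.9² = 103.9, so 104. The noncentral-t version gives 105 (power 0.801). Then 105 × 1.2 × 2 = 252. The plan's figures reproduce, and the calculation is for one two-group comparison of means after treatment.

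**2. What the ANOVA group effect estimates.** The article gives no trajectory for the effect, so these are assumptions. All have the effect rising linearly from 0 at baseline to 10.9 at week 6.

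| Assumed course after week 6 | Visits averaged | Group effect |
|---|---|---|
| not used | weeks 0, 2, 4, 6 | 10.9 × (0 + 1/3 + 2/3 + 1)/4 = 5.45 |
| held | all six | 10.9 × (0 + 1/3 + 2/3 + 1 + 1 + 1)/6 = 7.27 |
| half lost by 6 months | all six | (0 + 3.63 + 7.27 + 10.9 + 8.175 + 5.45)/6 = 5.90 |
| gone after week 6 | all six | (0 + 3.63 + 7.27 + 10.9 + 0 + 0)/6 = 3.63 |

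In each case the group effect is well below the 10.9 points at week 6.

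**3. Power of the two ANOVA tests.** Assume 105 per arm, equal between-visit correlation ρ of 0.6 to 0.9, the held course, no covariates, and a test against zero at two-sided 5%. Let k be the number of visits analysed.

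- Group effect: SE = 22.9 × √{[(1 + (k − 1)ρ)/k] × 2/105}. For k = 4 the SE is 2.64 to 3.04 and power 54% down to 43%. For k = 6 the SE is 2.58 to 3.03 and power 80% down to 67%.
- Group-by-time: noncentrality λ = (105/2) × Σ(dⱼ − mean d)² / [22.9² × (1 − ρ)], where dⱼ is the group difference at visit j. The sum of squares is 66.0 for k = 4 and 105.6 for k = 6. At ρ = 0.6, λ is 16.5 and 26.4, and power 94% and 99%. At ρ = 0.9 both exceed 99%.
- Plain week-6 comparison: 10.9 / [22.9 × √(2/105)] = 10.9/3.16 = 3.45, power about 93%.

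Low power is therefore not a general feature of the ANOVA branch. The test aimed at change is powerful under these assumptions. It still gives no week-6 difference and no interval for one.

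**4. Patients lost to incomplete rows.** The article gives no missingness pattern, so two are shown.

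- *Dropout only.* Spread the predicted 20% evenly over the five post-baseline visits, 4% at each. Week-6 scores: 252 × 0.88 = 222. All six visits complete: 252 × 0.80 = 202. The six-visit ANOVA loses about 20 patients who have the primary endpoint, 20/222 = 9%. An ANOVA on weeks 0 to 6 loses none of them.
- *Independent missed visits, 2% to 5% at each.* Of patients with a week-6 score, the six-visit ANOVA loses 1 − 0.98⁴ = 7.8% to 1 − 0.95⁴ = 18.5%. The weeks 0 to 6 version loses 1 − 0.98² = 4.0% to 1 − 0.95² = 9.8%.

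The loss thus runs from nothing to nearly a fifth, depending on which visits enter and how they are missed.

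**The case against.** Several points weigh on the other side.

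- **The ANOVA would be used for change, and its interaction test is powerful.** This stands (step 3). A reader might infer that the trial is badly underpowered from the 43% to 80% for the group effect. The article does not support that. It does not name the group effect as the primary test, those figures ignore the covariates listed in {20a}, and they test against zero rather than the margin of 3.
- **A week-6 contrast can be added to either model.** True, but none is stated, and an analyst who follows the text need not produce one.
- **A direct comparison may already be there.** If the t-test and Wilcoxon sentence covers outcomes, it allows a week-6 comparison. It may equally concern baseline only. On the first reading it adds further candidates; on the second, none addresses week 6.
- **All six visits is an inference.** {20a} speaks only of different time points; the six visits come from Trial design {8} and Table 2.
- **Intention-to-treat is promised, and imputation may be specified elsewhere.** So it is too strong to call this a flat contradiction of {20c}. Rows are lost only if nothing is imputed.
- **The analysts are third-party and blinded.** This limits choosing a method by its result, though it does not replace naming the method. A reader might want to put a figure on the inflated false-positive risk. Any such figure depends on which tests are counted as candidates, and the article does not settle that list.

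Leaving detail to an analysis plan does not answer the central point. The article is not silent: under a heading that covers the primary outcomes it states two non-equivalent methods, and a later plan could adopt either and comply.

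**Conclusion.** The point holds as a mismatch between endpoint and analysis. The primary outcome and the sample size concern one week-6 difference. The stated analysis is an open choice between two multi-visit methods, neither tied to week 6. The ANOVA branch, followed as written, gives either an average over visits or an omnibus test.

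The average would be about 5.5 to 7.3 points instead of 10.9 if the effect builds linearly to week 6 and holds and baseline is included. It would be as low as 3.6 over six visits if the effect vanished after week 6. These figures rest on assumed trajectories. Some patients with a week-6 score could also be dropped; the number cannot be fixed from the article.

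The documents do not support a claim that the planned analysis lacks power, or a particular false-positive rate.

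**What to change.** In {20a} and the abstract, delete the repeated-measures ANOVA option and name one primary analysis for each primary scale (WAB and CFCP):

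- a linear mixed model with visit as a category, group, group-by-visit, baseline score, the covariates already listed in {20a} (age, duration of illness, severity of aphasia) and an unstructured covariance;
- all randomised patients with available scores, analysed as randomised;
- the week-6 group contrast with its confidence interval as the primary result, judged for WAB-AQ against the margin of 3 in Sample size {14};
- contrasts at the other visits, including 6 months after onset, as secondary results from the same model.

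State as well whether the t-test and Wilcoxon sentence is for baseline description only.

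The cost is wording in the protocol and the analysis plan. No new data are needed, and the 105 per group need not change on this account, because that calculation already targets a single after-treatment difference.

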### Sample size {14}

Based on the previous pilot study, we expected that acupuncture combined with speech rehabilitation would be more effective than placebo combined with speech rehabilitation [6]. We were assuming that the difference in WAB-AQ values after treatment between acupuncture and placebo is 10.9, with a standard deviation of 22.9 in both groups. According to expert clinical observation, it was found that a superiority margin of 3 for comparisons of acupuncture and placebo for the primary outcome. We performed a superiority test to calculate the appropriate trial sample size with 80% power, *β* =0.2, and *α* = 0.05. The results showed that a clinically significant difference could be detected by a sample size of at least 105 in each group, allowing for a predicted 20% dropout rate. We plan to enroll 252 participants in this study.

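### The plan does not name baseline WAB-AQ or CFCP as a covariate, or fix how baseline enters the primary model, although both scores are collected and would add precision

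*Protocol article*

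**What the plan says.** - **Primary outcome** (Protocol article, Primary outcomes): "the difference between the two groups in WAB [17] scale scores and CFCP [18] scale scores after 6 weeks of treatment". This is a comparison of scores at one time point.
- **Sample size {14}**: it assumes that "the difference in WAB-AQ values after treatment between acupuncture and placebo is 10.9, with a standard deviation of 22.9 in both groups". The standard deviation is given with values after treatment, and no baseline correlation is used.
- **Model** (Statistical methods {20a}): repeated-measures ANOVA is one option; otherwise "linear mixed models were used to analyze changes in measurements at different time points". The section does not choose between the two. It also does not say whether the pre-treatment visit is a response, part of a change score, or neither.
- **Covariates** (same section): "Covariates such as age, duration of illness, and severity of aphasia will be included in the statistical model, correcting the effects of possible imbalances". Baseline WAB-AQ and baseline CFCP are not among the examples.
- **Data available** (Trial design {8}): "Six visits in total are scheduled for each subject at weeks 0, 2, 4, and 6", with two later visits. Table 2 marks WAB and CFCP at screening and at every visit after it.

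**The concern.** The protocol does more than leave covariates to a later document. It states what adjustment is for, gives examples, and omits the variable that would normally predict a patient's week-6 score best: the same score before treatment. It also describes the target in two ways, as week-6 scores in the outcome and sample-size sections and as changes over time in the analysis section. A raw week-6 comparison, a change-score comparison and a baseline-adjusted comparison can give different estimates and interval widths from the same data.

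At stake is the width of the interval to be compared with the superiority margin of 3, and how far a chance difference between arms at entry carries into the estimate. Severity of aphasia recovers part of this for WAB-AQ. It is likely to do less for CFCP, which measures functional communication in daily life.

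**Working it through.** **Inputs from the protocol (Sample size {14}).** Difference 10.9; margin 3, so the distance to be detected is 10.9 − 3 = 7.9; SD 22.9; α = 0.05 with sidedness not stated; power 80%; 105 per group; 252 in total; 20% dropout.

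**Assumptions not in the protocol.** r, the correlation of baseline with week-6 WAB-AQ; g, the correlation of the severity covariate with baseline WAB-AQ; severity carries no information on week 6 beyond baseline WAB-AQ; equal SDs at baseline and week 6 (for the change score).

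**1. Reproduce the plan's figure.** n per group = 2 × [(1.645 + 0.842) × 22.9 / 7.9]² = 103.9, so 104; the noncentral t gives 105. The stated 105 is therefore a one-sided 5% test with the unadjusted SD. The two-sided version needs 132 (133 by t). The design takes no credit for any covariate.

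**2. Patients left after dropout.** 252 × 0.8 = 201.6, about 101 per arm. Power = Φ(7.9 / (SD × √(2/101)) − 1.645). With SD 22.9 this is 79%.

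**3. Residual SD under each analysis.**
- Own baseline as covariate: 22.9 × √(1 − r²)
- Severity only: 22.9 × √(1 − (g·r)²)
- Change score, no covariates: 22.9 × √(2(1 − r))

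With g = 0.8 and one-sided 5%:

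| r | Severity only: SD, power | Own baseline: SD, power | Further variance cut | Change score: SD, power |
|---|---|---|---|---|
| 0.3 | 22.23, 81% | 21.85, 82% | 3% | 27.10, 67% |
| 0.5 | 20.99, 85% | 19.83, 88% | 11% | 22.90, 79% |
| 0.7 | 18.97, 91% | 16.35, 96% | 26% | 17.74, 94% |
| 0.8 | 17.60, 94% | 13.74, 99% | 39% | 14.48, 99% |

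**4. Sensitivity to g at r = 0.7.** The further cut in variance is 1 − (1 − 0.49)/(1 − 0.49g²).
- g = 0.6: 1 − 0.51/0.8236 = 38%
- g = 0.93: 1 − 0.51/0.5762 = 11%

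**5. Change score at r = 0.7.** Relative to the unadjusted variance, the change score leaves 2(1 − 0.7) = 0.60 and baseline adjustment leaves 0.51. The change score therefore captures 0.40 of a possible 0.49, about 82% of the gain. At r = 0.5 it leaves 1.00 and gains nothing; at r = 0.3 it is worse than no adjustment.

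**6. Chance imbalance that severity does not remove.** Its contribution to the estimate has SD 22.9 × r × √(1 − g²) × √(2/105). At r = 0.7 and g = 0.8 this is 22.9 × 0.7 × 0.6 × 0.138 = 1.3 points. Over r from 0.5 to 0.8 and g from 0.6 to 0.9 it runs from about 0.7 to 2.0 points.

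**The case against.** The covariates are given as examples, so baseline scores are not excluded, and an analysis plan that is not shown may name them. A repeated-measures or mixed model of changes over time may already carry the baseline visit as a response, in which case baseline information is used. The severity covariate is not defined: the eligibility criteria grade it 0–3, Secondary outcomes ties severity to the BDAE, and the Discussion says WAB itself assesses severity. Baseline WAB could be what is meant. The sample size does not rely on adjustment, so it is not undermined.

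All of this stands, and it rules out several stronger readings. A reader might infer that the plan discards the baseline scores; the text is silent and does not say so. A reader might infer that the covariate is certainly the four-level grade; that rests on an eligibility line. A reader might take 22.9 as the spread at entry; the protocol gives it only with post-treatment values. A reader might quote the rise from 79% to 88%, 96% or 99% at r = 0.5, 0.7 or 0.8; that comparator has no covariates, whereas the plan includes severity. A reader might also call the imbalance bias; under randomisation it is random error that the interval already reflects.

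The objection does not remove the point. The protocol addresses covariate adjustment and says what it is for. Its named examples do not secure adjustment for the outcome's own baseline, least of all for CFCP. An open list also leaves the primary covariates to be chosen later.

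**Conclusion.** The point holds as a gap in how the primary analysis is fixed, with a loss of precision that is conditional. If week-6 scores are modelled with only the named covariates, adding the outcome's own baseline at r = 0.7 cuts residual variance by a further 11% to 38% for severity correlations of 0.93 down to 0.6. At 0.8, one-sided power goes from about 91% to 96% with 101 per arm. At r = 0.3 the gain over severity is negligible. If the analysis is of change scores, most of the gain is already there at r = 0.7, but none at r = 0.5. If baseline is already a response in a suitably constrained mixed model, there is little left to gain and the remedy is only to say so.

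These figures rest on assumed correlations and, for the change score, on equal SDs. They concern WAB-AQ only, since the protocol gives no SD for CFCP. The change is worth making because it costs almost nothing. No error in the planned sample size and no systematic bias follows from this point.

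**What to change.** In Statistical methods {20a}:
- Define the primary estimate as the adjusted between-group difference in WAB-AQ at week 6, with baseline WAB-AQ as a continuous covariate. A mixed model with a common baseline mean in both arms is an equivalent choice.
- Do the same for CFCP with baseline CFCP, and for each secondary scale with its own baseline.
- Keep age, duration of illness and severity of aphasia, state which measure of severity is meant, and make the list closed.
- Report the adjusted difference with its confidence interval.

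Cost: wording, and one degree of freedom per model. The baseline scores are already scheduled, so no new data are needed, and the sample size need not change.

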### Interim analyses {21b}

Not applicable because we will not perform an interim analysis.

### Methods for additional analyses (e.g., subgroup analyses) {20b}

Not applicable because we will not perform additional analyses.

### Methods in analysis to handle protocol non-adherence and any statistical methods to handle missing data {20c}

Data may be missing. Therefore, we will analyze data based on intention-to-treat analysis (ITT) and per-protocol analysis (PP) principles. We will also assess the robustness of the results of our research by comparing the results of the two datasets mentioned above to evaluate group effects.

